## Abstract

**Background:**

There is emerging evidence that caesarean section in labour is associated with an increased risk of recurrent mid-trimester loss (MTL) and spontaneous preterm birth (sPTB) in subsequent pregnancies. This is likely due to inadvertent damage to the cervical tissue at the time of caesarean section. Transvaginal cerclage (TVC) has been demonstrated to be less successful in this high-risk cohort of women. However, transabdominal cerclage (TAC) may be more effective as the suture is placed above the level of cervical caesarean damage. A TAC can be placed before or during early pregnancy, although placement during pregnancy may be less effective. To determine the optimal clinical management for women with this risk factor, the ABOVE trial will evaluate the effectiveness of TAC compared to TVC in women who have experienced a MTL or sPTB following an in-labour caesarean section.

**Methods:**

ABOVE is a multicentre randomised control trial comparing TAC or TVC as a preventative strategy for sPTB in women with history of an in-labour CS and subsequent MTL (14^+ 0^ -23^+ 6^ weeks) or sPTB (< 30 weeks). Participants will be allocated to one of two groups - Group A (currently pregnant < 14 weeks’ gestation) and Group B (planning a pregnancy) - and randomised 1:1 to TAC or TVC within each group.

**Discussion:**

The ABOVE trial will investigate the efficacy of known interventions in the prevention of preterm birth, TVC and TAC, in women who have had a previous in-labour CS and subsequent MTL or sPTB. The trial will inform the development of evidence-based practice guidelines to optimise the care offered to this cohort of high-risk women. With escalating rates of CS and the increased recognition of the relationship between caesarean cervical damage and sPTB and MTL, this work is key.

**Trial registration:**

ISCRTN 10977996 (17/05/2024).

**Supplementary Information:**

The online version contains supplementary material available at 10.1186/s12884-026-08816-9.

## Background

There is increasing evidence that prior pregnancies ending with delivery by in-labour caesarean (CS) are associated with both spontaneous preterm birth(sPTB), i.e. delivery < 37 weeks completed gestation, and mid-trimester loss (MTL), i.e. pregnancy loss between 14 and 24 weeks, in subsequent pregnancies. A retrospective analysis of US cohort data demonstrated that full dilatation CS (FDCS) is associated with a six-fold increased risk of sPTB compared to first stage CS [1]. Adding to this concern is the high risk of a recurrent sPTB in this group of women [2, 3]. A recent study reported that the relative risk (RR) of recurrent sPTB at < 37 weeks gestation is 2.7 for all emergency caesarean sections (EMCS) and 3.1 for a full dilatation CS (FDCS), when compared to women with a prior sPTB and without EMCS as a risk factor [2]. This risk further increases when including MTL as an outcome, with 25.4% delivering at < 24 weeks of gestation (RR 5.65) [2]. Another study demonstrated a 41% absolute risk of recurrence of sPTB at < 30 weeks of gestation [3].

The relationship between sPTB, MTL and in-labour caesarean may be related to inadvertent cervical damage at the time of CS (cervical caesarean damage, CCD). At the time of in-labour caesarean, the surgical incision itself, or surgical site extensions, may be near or within the cervical tissue. This could disrupt the integrity of cervical tissue, leading to a cervical scar defect and resulting in compromised cervical function in future pregnancies [4]. The extent of CCD may also be influenced by the suture material at the time of caesarean section, the healing process and incidence of post-operative infection.Treatment modalities to reduce sPTB are currently limited but include cervical cerclage insertion [5]. There are three options for prophylactic suture placement: low vaginal or high vaginal cervical sutures (known as transvaginal cerclages - TVCs) or transabdominal cerclage (TAC). TVCs are placed during pregnancy, while TACs, placed at the level of the internal os, require laparotomy or laparoscopy either prior to pregnancy or in pregnancy [6]. In the UK, TACs are usually reserved for women who have had a trachelectomy or a failed vaginally placed cerclage, where they are known to be highly efficacious [6].

Treatment modalities to reduce sPTB are currently limited but include cervical cerclage insertion [5]. There are three options for prophylactic suture placement: low vaginal or high vaginal cervical sutures (known as transvaginal cerclages - TVCs) or transabdominal cerclage (TAC). TVCs are placed during pregnancy, while TACs, placed at the level of the internal os, require laparotomy or laparoscopy either prior to pregnancy or in pregnancy [6]. In the UK, TACs are usually reserved for women who have had a trachelectomy or a failed vaginally placed cerclage, where they are known to be highly efficacious [6].

TVCs are widely used to prevent sPTB in high-risk women [6]. However, retrospective studies show that they are ten-fold less effective in women who have had a sPTB following an in-labour CS, compared to other high-risk groups, with failure rates of 46% [4]. Conversely, TAC has a success rate of > 90% in high-risk women [7]. Another retrospective cohort study demonstrated that TAC was associated with less sPTB at < 30 weeks compared to TVC [8]. Moreover, women with a history of preterm birth and mid-trimester pregnancy loss report having a TAC in place reassuring [9].

Efficacy of TAC is thought to be related to the position of the suture above the scar. In pregnancy this may not be possible due to the implantation site and the inherent dangers of inserting a suture near the embryonic sac. Furthermore, increased vascularity in the pregnant cervix and an enlarged gravid uterus can make suture placement difficult. To date, there has been no comparison of outcomes from preconception and in-pregnancy TAC procedures.

In response to the accumulating, but often retrospective, evidence associating in-labour CS with MTL and sPTB, we have designed the ABOVE randomised control trial (RCT) to address this by comparing the effectiveness of TAC versus TVC in women who have had a previous sPTB or MTL following in-labour caesarean, both before and during pregnancy.

### Aim

The aim of this RCT is to reduce mid-trimester pregnancy loss and preterm birth in women with experience of MTL/sPTB after in-labour CS. The objectives of this study are:To evaluate the effectiveness of TACs in comparison with TVCs in women whohave experienced a MTL/sPTB following in-labour caesarean sectionTo compare pregnancy outcomes in women who had a TAC placed prior topregnancy with those where a TAC was placed in early pregnancy

### Design

ABOVE is a multicentre RCT comparing TAC and TVC as a preventative strategy for sPTB in women with history of an in-labour CS and subsequent MTL (between 14^+ 0^-23^+ 6^ weeks’ gestation) or sPTB (< 30 weeks’). Participants will be allocated to one of two groups - Group A (already pregnant) and Group B (planning a pregnancy) - and randomised 1:1 to TAC or TVC within each group. It is important to separately evaluate pre-conception and in-pregnancy TACs, as the suture can be placed higher pre-pregnancy and this may provide better support around cervical weakness caused by CCD. Therefore, the trial is separately powered for these two groups, and will require complete data from 160 participants (*n* = 80 in Group A, *n* = 80 in Group B).

### Participant recruitment

The target is to recruit over a period of 18 months. Potential participants will be identified from women referred to obstetricians or specialist preterm birth services who are based in one of the participating sites. These will be NHS hospitals in the UK (please refer to the ISRCTN record for participating sites). Eligible potential participants will be initially approached by clinicians when they attend for post-delivery debrief, pre-pregnancy counselling or specialist preterm service appointments. They will be given verbal information about the study. If willing, they will be contacted by the local research team, which may include attending clinicians and/or research midwives, who will provide the written information sheet and the opportunity to ask questions. Potential participants will be given sufficient time to consider taking part with the expectation that a decision will be made within a timeframe that will allow the arrangement of the allocated intervention to be carried out before they are 14^+ 0^ weeks pregnant. If a potential participant does not speak or understand English, a professional interpreter will be utilised to ensure all eligible women are given the option to participate and informed consent is obtained.

Group A: (in-pregnancy recruitment): eligible participants will be referred by clinical staff in the first trimester, e.g., first appointment with preterm specialist, and will be contacted soon afterwards by clinical research midwives.

Group B: (pre-conception recruitment): eligible participants will be identified by referral (with the woman’s permission) to the research team by clinical staff following a MTL or sPTB < 30 weeks’. These potential participants will then be approached by research midwives shortly after their NHS bereavement or post-partum debriefing consultant appointment, which is usually carried out six weeks after the event, or preconception counselling appointment which may happen at any time before a future pregnancy.

### Inclusion and exclusion criteria

Women will be eligible for the trial if they:

are willing and able to give informed consentare aged 16 or overhave had a previous in-labour caesarean section (between 4 cm and 10 cm (fully dilated) followed by a MTL (> 14 w) or preterm birth (< 30 weeks)are pregnant, but will be less than 14 + 0 weeks’ gestation at time of allocated intervention (Group A) ORare not yet pregnant but are considering a further pregnancy (Group B)

Potential participants will not be eligible for the trial if they:

are more than 14^+ 0^ weeks pregnant at time of randomisation (as insertion of TAC is associated with higher risk beyond this gestation)already have a cerclage or (Arabin) pessary in situare not planning another pregnancyhave a history of preterm birth (spontaneous/iatrogenic) prior to the in-labour caesarean sectionare pregnant and expecting more than one baby (multiple pregnancy)

### Randomisation and minimisation

Following written informed consent, participants (in either Group) will be randomised (1:1) to either TAC or TVC using a computer-generated randomisation procedure incorporated within the ABOVE trial database.

Recruiters and trial co-ordinators will not have access to the randomisation sequence. Due to the nature of the interventions, the study is not blinded to the care providers or participants; they will be informed at time of recruitment to which arm they have been randomised.

To ensure a balance between groups, randomisation will take account of whether the participant’s previous in-labour CS was carried out at 4–9 cm or at full dilatation (minimisation). This is because current thinking is that a CS at full dilatation is likely to be more damaging than one carried out earlier in labour. If a potential participant is unsure of her cervical dilatation at previous in-labour CS, further details will be sought from the hospital where the operation took place and if uncertainty remains, a decision will be made within the study team as to whether to include her in the study and if so, in which category she should be placed for the purposes of minimisation.

### Schedule of assessments

Following randomisation, the allocated procedure will be arranged. Participants in Group A will have the cerclage (TAC or TVC) inserted prior to 14 + 0 weeks’ gestation. Group B participants allocated to TAC will have the procedure placed before their next pregnancy and those allocated to TVC will have it placed during their next pregnancy before 14 + 0 weeks’ gestation. TACs are performed as an open or laparoscopic procedure under either regional or general anaesthetic, and may require an inpatient stay of up to three days. TVCs will be performed at the participant’s local maternity unit with the insertion technique and anaesthesia according to clinician’s discretion and local practices. TACs will usually remain in situ (to support any future pregnancies) while TVCs are removed at around 37 weeks’ gestation. TACs are more specialised procedures and so they may be carried out in designated specialist units, as per local practice. The timeframe between randomisation and study procedure is flexible from site to site, depending on theatre list availability, although all procedures must be carried out before the participant is 14 + 0 weeks’ pregnant.

### Follow up procedures

There are no trial specific follow up procedures. All other pregnancy care and special preterm prevention surveillance will continue according to local clinical protocols.

### End of study definition

To allow time for collection of outcome data and analysis, end of study is defined as is defined as six months after the expected date of delivery of the last participant recruited.

### Trial flowchart

See Fig. 1 for an illustration of participant flow through the study and anticipated number of participants.

**Fig. 1 Fig1:**
[figure not shown]
Trial flowchart (n=number)

### Outcome measures

#### Primary outcome

The occurrence of mid-trimester pregnancy loss or spontaneous preterm birth before 30 weeks of gestation.

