#### Secondary outcomes

Maternal:

Admission to hospital for symptoms of threatened preterm labourAdministration of antenatal corticosteroids for fetal lung maturationAdministration of magnesium sulphate for fetal cerebral protectionTransfer to other hospitals for neonatal cot availability (*in utero* transfer)Time between intervention and deliveryRequirement for additional emergency/rescue cerclageSerious complications occurring due to trial intervention: bladder injury, bowel injury, intraoperative rupture of membranes, cervical tear, hysterectomyMaternal sepsisAdmission to ITUMaternal death

Neonatal:

Gestation at birthBirthweightApgar scores (if available)Days before discharge home (up to 28 days)Admission to neonatal unitNeonatal infectionAny baby death

 ◦ *In utero* fetal death at or after 14 weeks◦ Stillbirth◦ Neonatal death

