### Data analysis

A data analysis plan has been prepared prior to commencement of study recruitment. Maternal, pregnancy, and surgical procedure characteristics will be presented with counts and percentages for categorical variables, mean and standard deviation for continuous Gaussian distributed variables, and median and interquartile range for continuous non-Gaussian variables.

All primary and secondary outcomes, and the components of the primary outcome will be summarised by treatment arm and Group (A or B) using frequencies and percentages.

In addition, relative risk will be calculated for the treatment effect (TAC vs. TVC) with 95% confidence intervals. An interaction test will be carried out to examine whether the treatment effect is significantly different between groups A or B. Where a difference is detected, separate relative risks will be presented for both groups. Where there is a significant treatment effect, Risk differences and Number Needed to Treat (NNT) will also be presented, with confidence intervals if significant. All these analyses will be corrected for the minimisation variable and Group (A or B).

The primary analyses will be by modified intention-to-treat for the pre-conception trial arms. Women who did not conceive, suffered an early miscarriage or are lost to follow-up will be excluded. A TVC will not be inserted in a non-pregnant patient (in line with standard clinical care) and therefore these participants will be removed from the trial, at the end of the 18-month recruitment period, so that the results relate to the number of stitches actually placed.

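### Cerclages placed in pregnancy go in before 14+0 weeks but losses count only from 14 weeks, so a procedure-related early loss enters no named comparison of the arms

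*Protocol article*

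**What the plan says.** The primary outcome is "The occurrence of mid-trimester pregnancy loss or spontaneous preterm birth before 30 weeks of gestation" (Protocol article, Primary outcome). The Background defines mid-trimester loss as "pregnancy loss between 14 and 24 weeks", and the Design section gives the range as 14+0 to 23+6.

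Under Schedule of assessments, "all procedures must be carried out before the participant is 14 + 0 weeks" of gestation. That limit covers three of the four randomised cells: Group A TAC, Group A TVC and Group B TVC. The fourth is different: "Group B participants allocated to TAC will have the procedure placed before their next pregnancy".

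Among the secondary outcomes, the in utero loss item is restricted to "fetal death at or after 14 weeks". The list of serious complications of the intervention includes intraoperative membrane rupture but not loss of the pregnancy.

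Under Data analysis, a paragraph that opens with the modified intention-to-treat approach for the pre-conception arms goes on: "Women who did not conceive, suffered an early miscarriage or are lost to follow-up will be excluded". No equivalent sentence covers a Group A woman who loses the pregnancy before 14+0.

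The Background, explaining why a TAC in pregnancy may not be placeable above the scar, mentions "the inherent dangers of inserting a suture near the embryonic sac".

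**The concern.** The period in which a procedure in pregnancy could cause a loss begins before the period in which the outcomes start to count losses. A pregnancy that ends between the procedure and 13+6 is not a primary event, not a fetal-death event and not a listed complication. Whether she stays in the denominator or is dropped, her loss is not compared between arms in any named outcome.

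This matters most in Group A, where an abdominal and a vaginal procedure are compared and both are done early in pregnancy. The article itself names a hazard close to the sac for the abdominal one. If in-pregnancy TAC causes more early loss than TVC, the reported effect would look better than the effect on keeping the pregnancy.

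It also bears on the second objective, which compares TAC placed before pregnancy with TAC placed in early pregnancy. Early procedural loss is one obvious way in which the two could differ.

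**Working it through.** **Inputs**
- Relative risk 0.33, from the 67% relative reduction under Power calculation; 40 women per arm, 80% power, 5% significance (taken as two-sided).
- TVC risk 41%: an assumption. The power section states no control rate. The Background gives 41% as a recurrence risk for birth before 30 weeks, and 46% as a TVC failure rate.
- Early-loss rate after the procedure: not in the documents, so shown as a range.

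**The plan's own figure.** TAC risk = 0.41 × 0.33 = 0.135. A two-sided 5% comparison of 41% with 13.5% (pooled variance) needs 41 per arm and has 79.9% power at 40. The planned 40 is reproduced if the control rate is about 41%. At 46% the power at 40 is 86.3%.

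**Group A.** Let *l* be the TAC-related loss before 14+0, with none from TVC, and *p* = 0.1353 the TAC risk from 14 weeks.
- All losses counted: RR = [*l* + (1 − *l*)*p*] / 0.41
- Early losses excluded: RR = *p* / 0.41 = 0.33
- Early losses kept as non-events: RR = (1 − *l*)*p* / 0.41

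| *l* | All counted | Excluded | Non-events | Power at 40 per arm, all counted |
|---|---|---|---|---|
| 5% | (0.05 + 0.95 × 0.1353)/0.41 = 0.1785/0.41 = 0.44 | 0.33 | 0.1285/0.41 = 0.31 | 63% |
| 10% | (0.10 + 0.90 × 0.1353)/0.41 = 0.2218/0.41 = 0.54 | 0.33 | 0.1218/0.41 = 0.30 | 44% |

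Five per cent of 40 is two women. With a TVC risk of 46% the all-counted figures are 0.42 and 0.51.

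If TAC had no benefit from 14 weeks (41% in both arms), 5% early loss gives (0.05 + 0.95 × 0.41)/0.41 = 1.07 when all losses count, against 1.00 if excluded and 0.95 if kept as non-events. At 10% the figures are 1.14, 1.00 and 0.90.

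**Group B.** Only TVC is placed in pregnancy. With a TVC-related early loss of 1%, 2% or 5% and none from the pre-conception TAC, the all-counted RR is 0.1353/(*l* + (1 − *l*) × 0.41) = 0.325, 0.321 or 0.308, against 0.33 with those women excluded as the plan states. The omission here works slightly against TAC.

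**Across Groups.** The two errors run in opposite directions. With 5% TAC loss in Group A and 2% TVC loss in Group B, the all-counted RRs are 0.435 and 0.321, a ratio of 1.36; with the losses excluded both are 0.33 and the ratio is 1. The planned interaction test between Groups, and the combined relative risk, can therefore be distorted too.

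**The case against.** **The outcome matches the aim.** The trial sets out to reduce mid-trimester loss and preterm birth, and the primary outcome measures exactly that. Widening it changes the question and costs power. With a background early loss of 5% or 10% in both arms and no procedural harm, the any-loss RR becomes (0.05 + 0.95 × 0.1353)/(0.05 + 0.95 × 0.41) = 0.41, or 0.47 at 10%, and power at 40 per arm falls from 80% to 72% or 65%. This stands, and it argues against replacing the primary outcome.

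**Early losses are not hidden from the trial.** Gestation at delivery is collected, time from intervention to delivery and intraoperative membrane rupture are secondary outcomes, and the data monitoring committee reviews serious adverse events. A procedure-related loss that completes at or after 14+0 is a primary event. A reader might infer that an early loss is invisible; the documents do not support that. What is missing is a named comparison by arm.

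**The Group A rule is not fixed.** A reader might infer that a Group A early loss counts as a success. No sentence says so: the stated exclusion belongs to the pre-conception arms, and the analysis plan, which is not shown, may settle Group A. The conclusion does not depend on it, because both handlings leave the loss out of the effect.

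**The direction is not general.** A reader might infer that the plan flatters the more invasive procedure throughout. It can do so only in Group A; in Group B the procedural effect runs the other way. An effect of a TAC already in place on early miscarriage in Group B would also go uncounted, but that is not a loss from a procedure in pregnancy.

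**The hazard is not quantified.** The Background names the danger to the sac as a reason why placement may be constrained; it reports no excess loss. The sizes above are illustrations.

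**Conclusion.** The gap is real and lies in text the article fixes: the time limit for procedures, the 14-week start of both loss outcomes, the complication list and the Group B exclusion. Losses between a procedure in pregnancy and 14+0 enter no named comparative outcome.

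If in-pregnancy TAC causes more early loss than TVC, the Group A result favours TAC: at an assumed 5% to 10% excess, an any-loss relative risk of about 0.44 to 0.54 would be reported as 0.33 or slightly lower. In Group B the distortion is smaller over the range shown and favours TVC. All of this rests on assumed early-loss rates, an assumed 41% TVC risk and the planned relative risk of 0.33; the documents do not show that any excess exists.

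This is a worthwhile, inexpensive improvement. It does not show that the primary outcome is invalid. Confidence is moderate, since the full protocol and analysis plan are not at hand.

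**What to change.** Keep the primary outcome as it is, and make three changes.

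1. Add a named key analysis beside it: any pregnancy loss at any gestation, or spontaneous birth before 30 weeks, counted from randomisation in Group A and from conception in Group B.
2. Keep every randomised Group A woman in that analysis, and state how a Group A loss before 14+0 is handled in the primary analysis.
3. Add pregnancy loss before 14+0, by arm and Group, to the secondary outcomes and to the complications of the intervention.

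The cost is mainly wording, because procedure details and gestation at delivery are already collected; recording of losses before 14 weeks should be confirmed. Background early miscarriages will add noise and lower the power of the any-loss analysis, which is why it should sit beside the primary outcome and not replace it.
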